##### Relationship between epidemiological and entomological endpoints for anopheline mosquitoes

To explore the relationship between the malaria hazard rate and the entomological endpoints, similar models as the cloglog models on the overall malaria infections will be applied to the epidemiological and entomological data in the clusters from which the entomological data are collected. The outcome is the time to malaria infections with relevant baseline covariates, random effect terms to account for the dependency within the same cluster and among the multiple malaria incidences from the same individual, and additional entomological covariates (HBR and mosquito density per light traps, respectively). The regression coefficient associated with an entomological covariate quantifies the change in the malaria hazard rate on the log scale, given one unit increase in the entomological covariate.

##### Subgroup PE analysis by age group

The above analysis of the first-time and overall malaria infections in the examination of the PE and diversion effect of SR will be based on all the subjects aged 6 months to 9 years 11 months. The same set of analyses will also be performed by two age subgroups: 6 months to 59 months old, and 60 months to 9 years 11 months old to examine if the PE and diversion effects of SR differs between the two age groups.

### Interim analyses {21b}

There will be one formal interim analysis to test the primary hypothesis. The decision boundaries at the interim analysis are calculated for either stopping for futility or stopping for efficacy using the O’Brien-Fleming error spending function [36, 38–41]. Since we adopt the non-binding futility boundary [42, 43], if it is decided the study will continue due to other considerations even if we cross the futility boundary at the interim look, there will be no inflation of type I error. In other words, the trial does not need to stop to accept the null hypothesis when the test statistic falls in the futility region at the interim stage. In addition, since trials submitted to VCAG are intended to demonstrate public health value, the committee strongly recommends trials are not stopped early for benefit. In our design setting, even if the efficacy boundary is crossed at the interim look, the study may continue and there will be no inflation of type I error, as efficacy is already established at the interim. The interim analysis will occur when 528 events (50% information) are collected.

If the interim result meets the stopping criterion for futility, that is, the one-sided *p*-value for Wald’s test on the log(HR) between SR and placebo at the interim is > 0.3450, the study may stop for futility. Since we adopt the non-binding futility boundary, if it is decided the study will continue due to other considerations even if we cross the futility boundary at the interim look, there will be no inflation of type I error. If the one-sided *p*-value < 0.00882, then the study can stop for efficacy; otherwise, the study will proceed. However, if it is decided the study will continue due to other considerations even if we cross the efficacy boundary at the interim look, there will be no inflation of type I error, as efficacy is already established at the interim.

If the one-sided *p*-value at the interim is > 0.00882 but < 0.3450, then the study will continue. At the final analysis, if the one-sided *p*-value from Wald’s test on the log(HR) between SR and placebo < 0.04668, we will reject the null hypothesis, claiming SR reduces the malaria hazard rate compared to placebo in Kenya at the significance level of 5%; otherwise, we will fail to reject the null hypothesis, claiming SR does not reduce the malaria hazard rate compared to placebo in Kenya.

Interim analysis data will be available to the DSMB, Funder, Sponsor, and SCJ along with the study oversight contractor, fhiClinical, and any ad hoc experts deemed appropriate. The DSMB has the ability to recommend stopping the trial based on safety concerns, but do not have the responsibility of stopping the trial due to their assessment of efficacy or futility. The responsibility to stop the trial is held by the Sponsor.

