#### Primary hypothesis on first-time malaria infection

The sample size determination on the required number of subjects (HHs) per cluster for testing the primary hypothesis is based on the hazard rate comparison in the proportional hazards regression model [36, 37]. With the following specifications: 1-sided type I error rate = 5%, true PE = 30%, a between-cluster CV of hazard rate = 44% (based on historical data collected from Kenya), one interim analysis for efficacy and non-binding futility with the O’Brien-Fleming error spending function when 50% of events have been collected then 1055 first-time malaria events will need to be observed to reach 85% power in testing the primary hypothesis on PE.

With a baseline first-time malaria infection hazard rate of 3.0 per person-year, 30 clusters per treatment arm, with 20 subjects (HHs) per cluster are expected to yield 1055 independent first-time malaria events within a 12-month follow-up period per cohort post randomization to yield 85% power. If, by the end of the 2-year study, 1055 independent malaria events are not reached, the study may extend until 1055 events are collected without inflating the type I error rate in the testing of the primary hypothesis. Factoring in a LTFU rate at 35%, the required sample size is 28 subjects (HHs) per cluster, which will be split in half between the two sequential cohorts with 14 subjects (HHs) per cohort per cluster.

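### The interim at 528 events carries more than 50% of the information (about 0.8 on the plan's full between-cluster CV), and the printed p-value thresholds do not come from the error spending function the plan names

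*Protocol article*

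**What the plan says.** The sample size section for the primary hypothesis assumes "1-sided type I error rate = 5%, true PE = 30%, a between-cluster CV of hazard rate = 44" percent, places one interim look "with the O’Brien-Fleming error spending function when 50% of events have been collected", and concludes that "1055 first-time malaria events will need to be observed to reach 85% power in testing the primary hypothesis on PE". It uses 30 clusters per arm and 20 evaluable children per cluster, split over two yearly cohorts drawn from the same clusters.

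The section on interim analyses {21b} describes the boundaries as "stopping for futility or stopping for efficacy using the O’Brien-Fleming error spending function" and states that "The interim analysis will occur when 528 events (50% information) are collected". It then prints fixed one-sided cut-offs: below 0.00882 for efficacy at the interim, above 0.3450 for non-binding futility, and at the final look, if the one-sided p-value on log HR "between SR and placebo < 0.04668, we will reject the null hypothesis".

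The primary analysis is a cloglog model with a random effect for cluster.

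**The concern.** There are two separate problems.

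- **Fraction.** The share of events equals the share of information only when the variance of log HR falls in proportion to 1/events. In a cluster trial part of that variance depends on the number of clusters. All 60 clusters are already contributing at the interim, so that part is fully present at 528 events and does not halve later.
- **Method.** A spending function and a set of fixed p-values are different rules. If the observed fraction is not 50%, they can point to different decisions on the same data, and the plan does not say which one governs.

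At stake are the interim efficacy and futility cut-offs, and a clear answer to which threshold applies at the end of a confirmatory trial meant for WHO review.

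**Working it through.** **Inputs** (sample size and interim sections): one-sided alpha 0.05; HR 0.70; CV 0.44, so CV² = 0.1936; 30 clusters per arm; 20 evaluable children per cluster; 1055 events in total; interim at 528; cut-offs 0.00882, 0.3450 and 0.04668.

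**1. The plan's event count depends on clustering.** Without clustering, Schoenfeld's formula gives 4(1.645 + 1.036)²/(ln 0.70)² = 226 events. The design effect is 1 + 19 × 0.1936 = 4.678, and 226.05 × 4.678 = 1057.5, against the stated 1055.

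**2. The stated power also depends on it.** Take Var(log HR) = 4/D + 2 × CV²/30, where D is the number of events.

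- At D = 1055: 0.0038 + 0.0129 = 0.0167, SE 0.129, drift 0.3567/0.129 = 2.76. Power with the printed bounds is 86.1%, against the stated 85%.
- With no cluster variance, power would exceed 99.9%.

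**3. Information at 528 events.** The variance is 0.0076 + 0.0129 = 0.0205. The fraction is t = 0.0167/0.0205 = 0.815. The plan's 50% is the bare event ratio, 528/1055 = 0.5005. On this variance formula, half of the information is reached at about 195 events.

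**4. Sensitivity of t.**

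| Assumption | t at 528 events |
|---|---|
| CV 0.44, cluster effects shared across years | 0.815 |
| Same, log-normal variance ln(1 + CV²) | 0.805 |
| Design effect recalculated at interim cluster size | 0.84 to 0.85 |
| Residual CV 0.3: 0.00979/0.01358 | 0.72 |
| CV 0.44, yearly cluster effects correlated 0.5, interim within cohort 1: 0.01347/0.02048 | 0.66 |
| Residual CV 0.2: 0.00646/0.01024 | 0.63 |
| No cluster variance, or independent yearly effects | 0.50 |

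Independent yearly effects would imply power of about 97%, which does not fit the plan's 85%.

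**5. Where the thresholds come from.** Classic two-look O'Brien-Fleming bounds are C/√t at the interim and C at the end. With t = 0.5 and one-sided alpha 0.05, C = 1.678.

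- Interim: 1.678/√0.5 = 2.373, p = 0.00882.
- Final: 1.678, p = 0.04668.
- The matching non-binding futility bound with beta 0.15 gives p = 0.3449, against 0.3450.

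**6. What the named function gives.** Lan-DeMets O'Brien-Fleming spends 2[1 − Φ(1.960/√t)] at the interim. The final p-value then brings total alpha to 5%.

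| t | Interim p | Final p |
|---|---|---|
| 0.50 | 0.0056 | 0.0482 |
| 0.63 | 0.0135 | 0.0459 |
| 0.72 | 0.0209 | 0.0439 |
| 0.815 | 0.030 | 0.0415 |
| Printed | 0.00882 | 0.04668 |

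A second version, which halves a two-sided 0.10 function, gives 0.0100 and 0.0460 at t = 0.5. It does not match either. The spending-type futility cut-off at t = 0.5 is about 0.40 to 0.43, not 0.3450.

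**7. Consequences of the printed pair** (bivariate normal, correlation √t).

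- Total alpha: 5.00% at t = 0.50, 4.88% at 0.63, 4.80% at 0.72, 4.72% at 0.815.
- Under PE 30% and drift 2.76, moving from t = 0.5 to 0.815: chance of an interim efficacy crossing 34% to 55%; chance of falling in the futility region 6.0% to 1.8%; power 86.3% to 86.1%.

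**The case against.** A reader might infer that the trial's error rates are broken. The documents do not support that. The printed pair keeps type I error at or below 5% at every fraction checked from 0.50 upward, and power agrees with the stated 85%. The thresholds are therefore exact only at 50%; they are not invalid elsewhere. The interim crossing and futility probabilities above are not stated in the protocol, so no stated figure is contradicted there, and the fall in false futility is favourable.

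A reader might also take 80% as established. It is not. The primary model includes baseline covariates, baseline incidence guides stratification, the CV is historical and to be re-evaluated at baseline, and incidence is expected to vary by year. Each of these could lower the fraction, so the range belongs with the figure.

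The practical effect is limited. Futility is non-binding, the study may continue after an efficacy crossing, and the protocol records that the WHO advisory group advises against stopping early for benefit. The printed p-values look operative as they stand, and at t = 0.5 the two methods' final thresholds are close (0.0467 and 0.0482). A rule for recalculating bounds may sit in an analysis plan or a monitoring charter that is not shown, so its absence is not the complaint.

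What remains is that this protocol itself states a fraction, a method and a set of numbers that do not agree with one another.

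**Conclusion.** The point holds in this form. On the plan's own CV and number of clusters, 528 events are expected to carry about 0.8 of the final information, not 0.5. This assumes that the full CV of 44% remains as residual variance and that cluster effects persist across both cohorts. Under the other assumptions tried, the fraction is about 0.63 to 0.72. It returns to 0.5 only with no cluster variance or with fully independent yearly effects, and neither fits the plan's own power.

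The thresholds are fixed two-look O'Brien-Fleming bounds, not the named spending function. This second part does not depend on the information fraction.

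The size is moderate. At t = 0.815 the interim efficacy cut-off is much stricter than the named function would set (0.00882 against about 0.030), and the final one is looser (0.04668 against 0.0415). An interim p of 0.015 or a final p of 0.045 would then be judged differently under the two rules. The futility cut-off is calibrated to the wrong fraction. Type I error is not inflated, and power is essentially as stated.

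**What to change.** - Define information as 1/SE² of log HR from the primary cluster model.
- Describe the interim as taking place at 50% of events, and give the expected information range (about 0.6 to 0.8, with the assumptions).
- Name one boundary method before any unblinded look. Either:
  - keep the fixed 0.00882 at the interim and recompute the final threshold at the observed information so that total alpha is 5% (0.0480 at t = 0.63, 0.0488 at 0.72, about 0.0495 at 0.815); or
  - apply the Lan-DeMets O'Brien-Fleming spending function at the observed information and drop the fixed p-values.
- Do not combine the two. At t = 0.815 a spending-function interim bound of 0.030 needs a final bound of 0.0415 to hold 5%, so pairing it with 0.04668 would exceed 5%.
- Restate the futility cut-off on the same basis, still non-binding.

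The cost is wording in the protocol or analysis plan and one recomputation of the boundaries at the interim. Recruitment, follow-up and data collection do not change.

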**Methods:**

This trial is designed as a cluster-randomized, placebo-controlled, double-blinded clinical trial. Sixty clusters will be randomly assigned in a 1:1 ratio to receive spatial repellent or placebo. A total of 6120 children aged ≥6 months to 10 years of age will be randomly selected from the study clusters, enrolled into an active cohort (baseline, cohort 1, and cohort 2), and sampled monthly to determine time to first infection by smear microscopy. Each cohort following the implementation of the intervention will be split into two groups, one to estimate direct effect of the spatial repellent and the other to estimate degree of diversion of mosquitoes and malaria transmission to unprotected persons. Malaria incidence in each cohort will be estimated and compared (primary indicator) to determine benefit of using a spatial repellent in a high, year-round malaria transmission setting. Mosquitoes will be collected monthly using CDC light traps to determine if there are entomological correlates of spatial repellent efficacy that may be useful for the evaluation of new spatial repellents. Quarterly human landing catches will assess behavioral effects of the intervention.

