## Statistical methods

### Statistical methods for primary and secondary outcomes {20a}

#### Primary hypothesis

H_0_: SR does not reduce the first-time malaria hazard rate compared to placebo in Kenya.

H_1_: SR reduces the first-time malaria hazard rate compared to placebo (first-time malaria hazard ratio between SR and placebo is < 1; the expected hazard ratio is 70% or PE is 30%.

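### A non-significant final result is to be read as a claim that the spatial repellent does not reduce malaria, which a superiority test with a 15% type II error cannot support

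*Protocol article*

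**What the plan says.** The last paragraph on the decision boundaries in the Protocol article, Interim analyses {21b}, sets the rule for the final analysis. The null is rejected if the one-sided Wald p-value on log(HR) is below 0.04668; "otherwise, we will fail to reject the null hypothesis, claiming SR does not reduce the malaria hazard rate compared to placebo in Kenya".

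Under Primary hypothesis (Statistical methods {20a}), the null is "SR does not reduce the first-time malaria hazard rate compared to placebo in Kenya". The alternative is a hazard ratio below 1, with 0.70 expected. Neither section gives an equivalence margin or a smallest PE worth having.

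The sample-size section for the primary hypothesis specifies a one-sided 5% error, true PE of 30% and a between-cluster CV of 44%. It then says "1055 first-time malaria events will need to be observed to reach 85% power in testing the primary hypothesis on PE".

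The analysis without baseline covariates will give hazard ratios with two-sided 90% confidence intervals. No conclusion is tied to those intervals. Section {21b} also describes a futility stop as accepting the null.

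**The concern.** A superiority test asks whether the data are hard to reconcile with no benefit. When they are not, the test is silent on whether benefit is absent. The rule nevertheless turns the unrejected null into a positive statement. To conclude that there is no worthwhile reduction, the interval would have to exclude a reduction of some pre-stated size, and the article names none.

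The result goes to the WHO Vector Control Advisory Group and is meant to inform a recommendation for the whole SR class. Between-cluster variation dominates the precision of this design, so intervals will be fairly wide. Applied as written, the rule would present an inconclusive trial to that audience as evidence that the product fails.

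**Working it through.** **Inputs.** From the sample-size section: 1055 events, CV 0.44, 30 clusters per arm, PE 30% (HR 0.70), power 85%. From {21b}: interim at 528 events (50% information), efficacy p < 0.00882, non-binding futility p > 0.3450, final p < 0.04668 (z = 1.678). Allocation is 1:1.

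**Assumption.** The article does not print its variance formula. An unclustered Schoenfeld calculation needs only 227 events, so 1055 must include a cluster term. I used the usual form:

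Var(log HR) = 2·CV²/c + 4/D = 2 × 0.44²/30 + 4/1055 = 0.0129 + 0.0038 = 0.0167, so SE = 0.129.

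**Reproducing the plan.** The stated boundaries give an overall one-sided type I error of 0.0500 with futility ignored. At PE 30% the standardised effect is 0.3567/0.129 = 2.76. Two-look power is 86.3% with futility ignored and 84.3% with it followed, against 85% stated. The type II error at PE 30% is therefore 13.7% to 15.7%.

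**Chance of not rejecting when the SR works.** For the final look alone this is Φ(1.678 − [−ln(1 − PE)]/0.129). The two-look figures use the bivariate normal with the stated boundaries.

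| True PE | Final look only | Two looks, futility ignored | Two looks, futility followed |
|---|---|---|---|
| 30% | 14.0% | 13.7% | 15.7% |
| 25% | 29.2% | 28.7% | 31.1% |
| 20% | 48.0% | 47.4% | 49.7% |
| 15% | 66.3% | 65.6% | 67.4% |
| 10% | 80.6% | 79.9% | 81.1% |

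The clause is written for the final look. The last column counts a futility stop as a non-rejection; in the column before it, every non-rejection occurs at the final look.

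**Sensitivity.** With ln(1 + CV²) in place of CV², SE is 0.125 and the 30% row becomes 11.7% (futility ignored) or 13.6% (followed). With the SE set to 0.128, so that power is exactly 85% with futility followed, the first four rows are 15.0%, 30.3%, 49.0% and 66.9%.

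**What non-significant results look like** (SE 0.129; half-width of the 90% interval 1.645 × 0.129 = 0.213 on the log scale):

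- Significance needs an observed HR below exp(−1.678 × 0.129) = 0.805, that is, PE above about 19.5%.
- Ruling out the 30% design effect needs an observed HR above 0.70 × exp(0.213) = 0.866. Between 0.805 and 0.866 the result is not significant and 30% PE is still inside the interval.
- HR 0.82 gives one-sided p = 0.062 and 90% CI 0.66 to 1.01.
- HR exactly 1.00 gives 90% CI 0.81 to 1.24, which still leaves room for a reduction of about 19%.

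**The case against.** The operative step, not rejecting, is correct. The words after it may only name the hypothesis left standing, since they closely follow the wording of the null. The clause is a testing rule rather than a reporting rule. The primary objective includes quantifying PE, and 90% intervals are planned for the unadjusted analysis. In the Background the authors themselves treat the non-significant Indonesian trial (27.7% reduction for first events) as underpowered, not as showing no effect. The probabilities above are the ordinary type II error curve of any design with this precision, and rewording changes none of them. They also rest on a variance formula that the article does not give; across variants, the events needed for 85% power run from about 710 to 1170.

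Much of this stands. The fault is confined to one clause and to interpretation, the planned intervals would soften the harm, and the curve measures how often the clause would mislead rather than a defect in the design. It does not rescue the clause. Nothing elsewhere withdraws it, the intervals are not linked to the conclusion, and the 85% power alone shows the claim is unsupported. The treatment of the Indonesian trial counts against the rule, because the same kind of result here would be declared no reduction.

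**Conclusion.** The concern holds. The rule as written draws a negative conclusion that the test cannot support. At the design effect it would be wrong about 15% of the time on the plan's own power (13.7% to 15.7% recomputed). At true PE of 20% it would be wrong about half the time, and at 15% about two-thirds. The figures below PE 30% depend on the assumed clustered variance; the finding itself does not. Type I error, power, boundaries and sample size are unaffected. The clause should be changed because of the policy use planned for the result.

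**What to change.** Replace the final clause in {21b} with wording such as:

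> Otherwise the null hypothesis is not rejected and the trial has not demonstrated a reduction. PE is reported with its confidence interval, and effects are described as ruled out only where the interval excludes them.

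This avoids calling every non-significant result inconclusive, since some intervals may exclude any worthwhile effect. The futility wording that speaks of accepting the null should be brought into line.

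The rewording costs one sentence and needs no extra data or participants. If the sponsor wants to be able to make a negative claim, it should do so only when the upper confidence limit for PE lies below a minimum worthwhile PE fixed before unblinding. Choosing that value is a substantive decision. It should allow for the precision available: even an observed HR of 1.00 rules out only PE above about 19%.

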## Assignment of interventions: Blinding

### Who will be blinded {17a}

All participants, investigators, and study staff will be blinded to cluster, thus HH, allocation throughout the duration of the trial.

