## Oversight and monitoring

### Composition of the coordinating center and trial steering committee {5d}

UND serves are the lead organization and assumes the overall responsibility for management, oversight, and administration for the program. The coordinating personnel at UND include the Lead PI, Scientific Director, Program Manager, Program Coordinator, and Finance Manager. UND communicates on a day-to-day basis with KEMRI and CDC. KEMRI is responsible for running the cRCT on a day-to-day basis which includes but is not limited to conducting a baseline survey, deploying SRs, entomological monitoring, and subject follow-up. CDC provides technical support for the entomological and epidemiological aspects of the study. Representatives from KEMRI, CDC, and UND serve on the data management team overseeing the development and implementation of data collection, recording, and cleaning. UND will rely on fhiClinical to provide clinical oversight and monitoring of study processes, which includes but is not limited to checking enrolment, training of staff on GCP, ensuring subjects are properly consented, data are appropriately gathered, data quality, safety events are documented and reported as required, investigational product is stored, distributed and managed per specifications, and study close-out activities occur on a timely basis.

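### Comparative interim results go to the sponsor that runs the trial, the funder, SCJ and the monitoring contractor, with no stated firewall and all of cohort 2 still to come

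*Protocol article*

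**What the plan says.** Interim analyses {21b} sets one formal look at 528 first-time events. The statistic is a one-sided Wald test of the log hazard ratio, read against two boundaries:

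- Futility: "on the log(HR) between SR and placebo at the interim is > 0.3450, the study may stop for futility".
- Efficacy: one-sided p "< 0.00882, then the study can stop for efficacy; otherwise, the study will proceed".
- At the final analysis the threshold is one-sided p "< 0.04668, we will reject the null hypothesis".

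The same section then says who sees the result: "Interim analysis data will be available to the DSMB, Funder, Sponsor, and SCJ along with the study oversight contractor, fhiClinical", together with any ad hoc experts. The DSMB may recommend stopping on safety grounds but is not responsible for stopping on efficacy or futility: "The responsibility to stop the trial is held by the Sponsor".

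The section on the data monitoring committee {21a} names UND as the Sponsor. Composition of the coordinating center {5d} makes UND responsible for managing the programme and adds: "The coordinating personnel at UND include the Lead PI, Scientific Director, Program Manager, Program Coordinator, and Finance Manager". The contractor carries out the clinical monitoring ({5d} and {23}).

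On blinding, {17a} states: "All participants, investigators, and study staff will be blinded to cluster, thus HH, allocation throughout the duration of the trial". Concealment mechanism {16b} says the same of investigators, and it keeps the study biostatistician blinded until database lock.

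On duration, the sample size section for the primary hypothesis says that if 1055 events are not reached in two years, "the study may extend until 1055 events are collected without inflating the type I error rate".

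**The concern.** The interim result is comparative and directional: one p-value is judged against an efficacy limit at one end and a futility limit at the other. Coding the arms would not hide the answer from a body that has to act on it. As written, the organisation that leads the trial sees the treatment effect while most of the follow-up is still ahead.

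That knowledge could colour whether the study stops, continues past a boundary or is extended. It could also colour choices the article leaves open until the end, such as which baseline covariates enter the primary model. The results are intended for the WHO Vector Control Advisory Group, and a reader there could fairly ask whether such decisions were made with the answer in view. The exposure cannot be undone once the look has taken place.

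**Working it through.** **1. Is the interim a real comparative test?** Reproduce its boundaries. A classic two-look O'Brien-Fleming design with one-sided alpha 0.05 and equal information has critical values c√2 and c. Here c solves 1 − P(Z₁ < c√2, Z₂ < c) = 0.05, with corr(Z₁, Z₂) = √0.5. The solution is c = 1.678 and c√2 = 2.373, so the p-values are 0.04668 and 0.00882. Both match the article. The interim is a full efficacy and futility comparison.

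**2. Set the passages side by side.**

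| Question | Article | Section |
|---|---|---|
| Who sees interim results? | DSMB, funder, Sponsor, SCJ, contractor, ad hoc experts | {21b} |
| Who decides on stopping? | Sponsor | {21b} |
| Who is the Sponsor? | UND | {21a} |
| What does UND do? | Manages the programme; its staff include the Lead PI | {5d} |
| Who stays blinded to allocation? | Participants, investigators, staff, study biostatistician | {16b}, {17a} |

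No section separates those at UND who see the interim from those who run the trial.

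**3. When does the look fall?** Inputs:

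- Cohort 1 core children: 14 per cluster × 60 clusters = 840 (Trial design {8}).
- Placebo hazard 3.0 per person-year and PE 30%, so the repellent hazard is 0.70 × 3.0 = 2.1 (Sample size {14}).
- Loss to follow-up 35%, treated here as an annual dropout hazard δ = −ln(0.65) = 0.431 (assumption).
- Simultaneous enrolment and immediate detection (assumptions).

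Without loss, solve 840 × [1 − (e^(−3.0t) + e^(−2.1t))/2] = 528. This gives t = 4.7 months, with 19.3 of 24 months left.

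With loss, each arm contributes λ/(λ+δ) × [1 − e^(−(λ+δ)t)]. This gives t = 5.4 months, with 18.6 left.

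The table varies the placebo hazard over 2.5 to 4.1, the local infection incidence range in Study setting {9}. It also shows the effect of adding a gamma cluster frailty with CV 44%.

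| Placebo hazard | Months to 528 events | Months left of 24 |
|---|---|---|
| 2.5, loss, frailty | 7.7 | 16.3 |
| 3.0, no loss, no frailty | 4.7 | 19.3 |
| 3.0, loss, frailty | 6.2 | 17.8 |
| 4.1, no loss, no frailty | 3.5 | 20.5 |

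Independently of this model, Participant timeline {13} puts the interim with intervention in the August 2021 to July 2022 column. All of cohort 2 therefore follows it.

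**4. How much does the look reveal?** The plan's label is 528/1055 = 50%. With clustering, Var(log HR) = 4/D + 2·CV²/30, where D is the number of events and 30 the clusters per arm:

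- D = 528: 0.00758 + 0.01291 = 0.02048, SE 0.143.
- D = 1055: 0.00379 + 0.01291 = 0.01670, SE 0.129.
- Information fraction: 0.01670/0.02048 = 0.815 (0.805 with ln(1+CV²) in place of CV²).

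Conditional power under the observed trend, against the final threshold:

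| Interim one-sided p | 50% information | About 80% information |
|---|---|---|
| 0.00882 | 0.99 | 0.99 |
| 0.345 | 0.06 | 0.002 |

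A result at either boundary largely foretells the outcome on either reading.

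**5. Would the extension be used?** At 3.0 and 2.1 per person-year, two cohorts of 840 followed for 12 months each give about 1,535 first events without loss and about 1,352 with it. Only if 35% contribute no follow-up at all (546 children per cohort) does the total fall to about 998, just short of 1055.

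**The case against.** **Blinding covers allocation only.** The statements in {16b} and {17a} concern which cluster received which product, and {21b} does not say that codes are released. A pooled hazard ratio does not identify a household's arm. This stands: a reader might infer an outright contradiction, but the text supports only a strong tension.

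**The people in the field are not on the list.** KEMRI runs deployment and follow-up day to day ({5d}) and is not a named recipient. Without codes nobody could treat the arms differently. A reader might infer biased product replacement or visit intensity, and the article does not support that. The exposure is at programme level.

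**Type I error.** A reader might infer that disclosure, or an extension, inflates alpha. Disclosure alone does not, and neither does running to a fixed target of 1055 events. A narrow gap remains because extension is optional. Suppose a decision-maker who has seen the interim could choose between ending at 800 events and running to 1055. The worst-case one-sided alpha would rise from 0.050 to about 0.055 at 50% information, and from 0.047 to about 0.050 with the full clustering variance. Since about 1,350 events are expected with loss, the choice would probably not arise.

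**The 80% figure.** Baseline covariates in the model ({20a}) and stratification guided by baseline incidence ({16a}) could reduce the residual cluster variance and move the fraction towards 50%. This stands, so 80% is an upper figure.

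**Other limits.** SCJ is only expanded as a company name in the text shown; its role as manufacturer would be an inference. The DSMB also reviews study quality and does receive the interim data. Its charter is not shown and may hold more detail, but it would have to override an explicit access list to remove the problem. The article's reluctance to stop early for benefit is a reason not to tie stopping to the boundary. It is not a reason for wide access to the result.

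**Conclusion.** The point holds as one of access and governance. The article gives a directional comparative result to the body that manages the trial, houses the Lead PI and decides on stopping, and to the funder, SCJ and the monitoring contractor. It states no firewall. This undermines the blinding it promises to investigators, even though allocation codes are not said to be released.

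The look comes about 5 months into cohort 1 at design rates, with roughly 16 to 20 of 24 intervention months left over the documents' incidence range. That rests on exponential hazards, simultaneous enrolment and immediate detection; monthly smears, double reading and staggered entry could shorten the remainder by about a month. That cohort 2 follows entirely needs none of these assumptions. The information seen is 50% by the plan's label and about 80% if the whole 44% CV remains unexplained; the point stands at 50%. The harm is to programme decisions, analysis choices and credibility, and the nominal error rate is not affected by the disclosure itself.

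**What to change.** Amend Interim analyses {21b}, and the DSMB charter to match:

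- Arm-level interim results go only to the DSMB and its independent statistician, a role that {21a} already provides.
- They apply the stated boundaries and send the Sponsor one of three messages: continue, futility crossed, or efficacy crossed. The Sponsor keeps the final decision.
- The funder, SCJ, the contractor and UND trial personnel see only pooled, blinded data until database lock.
- Any extension to 1055 events is decided on the pooled event count alone.

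Sample size, boundaries and trial procedures do not change. The cost is protocol and charter wording, and the Sponsor would decide on a recommendation without seeing the comparative data. The amendment must be in force before the 528th event.
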